## Measures

### Primary outcomes

#### Parenting stress

The parenting stress index/short form (PSI/SF; Abidin, 1986) assesses self-reported PS with 36 items. Items are rated on a five-point Likert scale from 1 (strongly disagree) to 5 (strongly agree). The Chinese version is consistent with the original structure and the internal consistency of Chinese version of the total scale was 0.93, with 0.85 for Parental Distress scale, 0.86 for Parent-Child Dysfunctional Interaction scale, and 0.87 for Difficult Child scale (Ren, 1995).

### Secondary outcomes

(1) Additional parent-, child-, and parent–child relationship-related correlates.

#### Child behavior difficulties

Strengths and difficulties questionnaire (SDQ; Goodman, 1997) assess five sub-scales (hyperactivity, emotional, conduct problems, problems with peers and prosocial), each of them includes five items. The questionnaire asks parents to rate their child's emotional and behavioral problems on a 3-point Likert scale (ranging from 0 = not ture to 2 = certainly true). The Cronbach's α of Chinese version were ranging between 0.30 and 0.83. The reliability was 0.40–0.79 (Du et al., 2008).

#### Temperament of child

Emotionality, activity and sociability temperament inventory (EAS; Buss and Plomin, 1986) includes three scales that assess parents' perceptions of their children's emotionality, activity level, and sociability. It is composed of 20 items, rated on 5-point scale anchored by 1 (not typical of child) and 5 (very typical of child). It was demonstrated the adequacy of parent perceptions as general valid measures of children's temperament (Slabach et al., 1991; Porter et al., 2005).

#### Parental mentalizing

Parental reflective functioning questionnaire (PRFQ; Luyten et al., 2017) assesses three scales with 18 items: (1) interest and curiosity in mental states (IC), (2) certainty of mental states (CMS), and (3) prementalizing (PM), which signifies deficits in parental reflective functioning (PRF). Items are rated on a 7-point Likert scale ranging from “strongly disagree” to “strongly agree.” The three-factor model of Chinese vision had a good fit and criterion-related validity (Ye et al., 2022).

#### Parental self-efficacy

Brief parental self-efficacy scale (BPSES; Woolgar et al., 2023) is a 5-item scale, which measures how confident parents are that they can manage the tasks and demands of parenting. Each item on a five-point Likert scale: strongly disagree; disagree; neutral; agree; strongly agree (corresponding to scores 1 to 5, respectively). This study marks the first administration of this questionnaire in China. A Chinese version was translated for this purpose and demonstrated good reliability.

#### Parental personality functioning

Level of personality functioning scale-brief form 2.0 (LPFS; Weekers et al., 2019) is a 12-item scale. Each item is rated on a 4-point scale from 1 (very false or often false), 2 (sometimes false or somewhat false), 3 (sometimes true or somewhat true) to 4 (very true or often true). It assesses personality functioning, with higher scores indicating more impaired personality functioning. The Chinese version of this scale had good reliability (Cheng et al., 2025).

#### Parental mental health

The patient health questionnaire is a DSM-IV-based screening tool for the diagnosis of mental disorders. This study used a 9-item depression module (PHQ-D) and a 7-item generalized anxiety module (GAD-7). Participants rated the frequency of symptoms over the past 2 weeks on a 4-point Likert scale (1 = not at all, 4 = much more than usual). The Chinese version of the scale was reported to have good reliability (Yu et al., 2012).

#### Parents–child relationship quality

The multiperspective parent–child relationship questionnaire (M-PCR; Müller and Achtergarde, 2018) contains 14 items for each rater on a five-point Likert scale (0 = I disagree; 4 = I agree totally) and provides subscale scores for the contents of affective bond and functional-conflict, which are aggregated in the main M-PCR score. As no Chinese version of this questionnaire existed, it was translated and revised for the present study. The translated version demonstrated excellent reliability, and its use was formally approved by the original developers.

#### Satisfaction

Questionnaire to measure patient satisfaction-8 (ZUF-8 Questionnaire; Schmidt and Nübling, 2002) is a method of documenting overall patient satisfaction at the conclusion of hospitalization. Each of the eight items is scored on a 4-point scale (1 = poor, 4 = excellent), four of which are reverse scored and summed to form a total scale with a total score of 32. The instrument is frequently utilized in surveys assessing satisfaction with interventions. It is also frequently used in surveys related to satisfaction with the quality, contents, and effects of the intervention. The internal consistency (Cronbach's alpha) was between 0.87 and 0.93 for the individual samples and 0.92 for the total sample of the above-mentioned routinized patient surveys (*n* = 6,865). The values for split-half reliability and parallel test reliability were equally high.

Table 1 shows a detailed outline of the planned measures at each follow-up point throughout the trial.

**Table 1 T1:** Schedule of assessment administration for a randomized controlled trial of LPP.

Construct	Instrument	Items	Pre-test	Post-test	Follow-up
Parental stress	Parenting Stress Index-Short Form (PSI-SF)	36	×	×	×
Child behavior difficulties	Strengths and difficulties questionnaire (SDQ)	25	×	×	×
Temperament of child	Emotionality, activity and sociability temperament inventory (EAS)	20	×	×	×
Parental mentalising	Parental reflective functioning questionnaire (PRFQ)	18	×	×	×
Parental self-efficacy	Brief parental self-efficacy scale (BPSES)	5	×	×	×
Parental personality	Level of personality functioning scale-brief form 2.0 (LPFS)	12	×	×	×
Parental mental health	Brief patient health questionnaire (Brief PHQ)	16	×	×	×
Parents–child relationship quality	Multiperspective parent–child relationship questionnaire (M-PCR)	18	×	×	×
Satisfaction	Questionnaire to measure patient satisfaction-8 (ZUF-8)	8		×	

#### Subjective experience of participation

One-to-one semi-structured interviews will be conducted to explore the subjective experience of the LPP. The interviews was employed in a similar intervention project in Germany (Georg et al., 2022), the subsequent questions explored the following topics utilizing open-ended and closed-ended questions: expectations before treatment, the therapeutic relationship, interventions and significant moments, outcomes and termination of therapy. After each question, parents will be encouraged to give examples or mention specific situations to illustrate their experiences. Further probes will be used by the interviewers to clarify ambiguities.

(2) Recruitment rates for each recruitment methods, retention rates, dropout rates, compliance rates, etc.

**Recruitment, retention, and intervention completion**: the proportion of parents screened relative to those enrolled; the proportion of enrolled parents who completed the intervention; dropout rates; and reported reasons for attrition.

**Program compliance**: session attendance, including the number of group and individual sessions attended per participant.

**Influencing factors**: factors of retention and effectiveness of the intervention.

### Assessment of treatment fidelity

The project leader, a researcher in the IPP, specializing completed formal LPP training and participated in multiple intervention sessions in Germany. Prior to the implementation of the program in China, the project team conducted a cultural adaptation of the LPP (Hu et al., in prep), with ongoing supervision provided by the original German LPP team. Based on the results of thematic analysis of data collected from community stakeholders, cultural adaptation was further explored using an integrative theoretical framework combining the cultural adaptation process model (comprising preparation, collaborative implementation, and iterative refinement) and the ecological validity model (including language, persons, metaphors, content, concepts, goals, methods, and context). While certain peripheral components of LPP were adapted to align with the needs and realities of the new target group, the core components—enhancing parents' mentalized understanding of their children's emotions and breaking the intergenerational transmission of attachment trauma—were consistently retained and emphasized. Following cultural adaptation, the program was tailored to the daily circumstances of Chinese parents to minimize any sense of distance from an intervention originating in a different cultural context. For instance, childhood objects used to prompt recall of early experiences were adapted: items unfamiliar to Chinese parents were replaced with culturally meaningful counterparts from their own childhoods, while retaining the original symbolic significance. To ensure treatment fidelity, all intervention sessions will be video-recorded and reviewed as part of regular supervision.

### Data collection procedure

Subsequent to enrollment and the provision of informed consent, parents will be invited to the site where the intervention will be administered to participate in the questionnaire assessment and interview on-site (T0). Parents eligible to participate will then be randomly assigned to either the treatment immediate group (TI) or the waitlist control group (WL). Participants in the WL group were offered to participate in the intervention after a 2-months observation period. During this 2-month period, TI group received the full intervention and completed the posttest at the conclusion of this period. Prior to the WL intervention, participants in both groups will receive a second questionnaire assessment (T1). Subsequent to the WL's completion of the intervention, a third questionnaire assessment will be conducted (T2). At subsequent follow-ups, both groups will continue to complete two assessments (T3 and T4) at 3- and 9-months post-intervention.

### Statistical analysis

All parents assessed at baseline (T0) will be included in the data analysis following intent-to-treat principles. Sociodemographic variables and baseline assessment data will be used to characterize the enrolled sample. Descriptive data on recruitment, dropout, and retention rates will also be collected. Additionally, qualitative data—including reasons for dropout—will be analyzed to evaluate the appropriateness and acceptability of the study procedures and intervention. The primary objective of this study is to examine changes in participant's parenting stress and other parenting-related correlates (e.g., parental mentalizing, personality functioning, self-efficacy, and mental health), parent-child relationship quality, and children's variables (e.g., child's behavior difficulties and temperament) before and after the intervention, measured by standardized questionnaires. Participant satisfaction will be assessed using a standardized questionnaire. Furthermore, parents' subjective experiences during the LPP will be explored through semi-structured interviews. The quantitative data will be analyzed using SPSS 21.0 (IBM Corp., Armonk, NY, USA), employing repeated measures ANOVA (rmANOVA), *t*-tests, and chi-squared tests. The analysis of qualitative data will be conducted using the grounded theory methodology.

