### Inclusion and exclusion criteria

The study further aims to examine whether the LPP, in addition to reducing parenting stress, may exert a preliminary preventive effect on children's mental health risk. As the optimal age for prevention falls below 14 years, this cutoff was applied. To balance heterogeneity of developmental characteristics, measurement coverage and feasibility of parental participation, the child age range was set from 4 to 14 years. Eligible participants are parents of children aged 4 to 14 years experiencing elevated parenting stress, defined as a Parenting Stress Index (PSI) score ≥ 85 (critical high level) with informed consent. Exclusion criteria included: (1) serious physical illness (e.g., cancer), (2) active severe mental illness, and (3) communication difficulties or language barriers that would prevent meaningful participation in a group-based intervention.

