### Sample size

The determination of these parameters was facilitated by the utilization of the PASS 15.0 (NCSS Statistical Software, East Kaysville, UT, USA) software. Preliminary studies in the field have indicated a decline in the values of the indicators—total stress of PSI in the LPP intervention group, with a mean decrease of 11.3, and a corresponding decrease in the control group, with a mean decrease of 3.1 based on a previous MBT-based early intervention study (Fonagy et al., 2016). The experimental design employed a parallel approach, with the groups assigned in a 1:1 ratio. Given the exploratory nature of this study and resource constraints, a relatively liberal alpha level of 0.1 was adopted for sample size estimation. The clinical threshold of non-inferiority was set at 10% and the power level was set at 0.8. PASS15.0 calculated a total of 20 cases for each group. In the preparatory phase for this RCT, a pilot trial was conducted with a small cohort of five parents. As a zero dropout rate was observed in this pilot, no oversampling to compensate for participant attrition was deemed necessary. However, based on attrition rates observed in a comparable Chinese trial and accounting for the waitlist-control design, we conservatively estimated an attrition rate of approximately 10% (Jiang et al., 2024). Consequently, a minimum total sample size of 44 participants (22 per group) was determined to be required.

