### Randomization

Randomization will occur immediately following the completion of baseline assessment. Eligible participants will be assigned in a 1:1 ratio to either the immediate intervention group or a waitlist control group using a computer-generated sequence with random block sizes of 4 and 6. Stratification was not performed given the exploratory nature of the study and the anticipated sample size. An independent data manager generated the allocation sequence, and participant enrollment was conducted by a clinical interviewer, who then accessed a secure web-based system to obtain the treatment assignment. Baseline comparability between conditions will be examined on key demographic and clinical variables. Participant blinding is not feasible, as individuals must be informed whether they will begin the intervention immediately or after a 2-month delay.

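### The intent-to-treat promise is not delivered by repeated-measures ANOVA, and the analysis set is defined by the T0 assessment instead of by randomisation

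*Protocol article*

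**What the plan says.** Three parts of the protocol article bear on this.

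- **Analysis set and method (Statistical analysis).** The set is fixed as "All parents assessed at baseline (T0) will be included in the data analysis following intent-to-treat principles". The quantitative methods follow in the same paragraph: SPSS 21.0, "employing repeated measures ANOVA (rmANOVA), *t*-tests, and chi-squared tests". No mixed model or imputation is named.
- **Attrition (Sample size).** A five-parent pilot lost nobody. Citing a comparable Chinese trial, the authors nevertheless write "we conservatively estimated an attrition rate of approximately 10" per cent, and raise 20 per group to 22.
- **Order of events (Randomization; Data collection procedure; Inclusion and exclusion criteria).** "Randomization will occur immediately following the completion of baseline assessment", and "Eligible participants will be assigned in a 1:1 ratio to either the immediate intervention group or a waitlist control group". Data collection procedure gives the same order: T0 takes place, and only then are eligible parents allocated. Eligibility rests on elevated stress, "defined as a Parenting Stress Index (PSI) score ≥ 85 (critical high level) with informed consent". Table 1 lists the PSI-SF among the pre-test instruments.

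The primary question is whether PSI falls more in TI than in WL after the five-week programme. WL parents start the programme after T1, so T0-T1 is the randomised comparison of treated with untreated parents.

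**The concern.** The article commits both to a set of parents and to a method, and once any T1 data are missing the method does not cover the set. A published result would be described as intent-to-treat while resting on parents with complete data.

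That matters because the reasons for leaving may differ between the arms. Parents know their allocation; TI asks for ten sessions in five weeks, and WL asks for a two-month wait. Completers in the two arms need not be comparable, and the randomisation no longer protects the contrast.

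The definition of the set is a separate and smaller fault. A parent who is assessed at T0 but found ineligible, or who withdraws before allocation, belongs to the stated set yet has no arm in which to be analysed.

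**Working it through.** **Inputs** (all from Sample size unless noted): 20 per group before attrition; attrition about 10%; total 44; mean PSI decrease 11.3 (LPP) and 3.1 (control). Waves T0 to T4 come from Data collection procedure.

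1. **The plan's own figure.** 20 × 1.10 = 22 per group, and 2 × 22 = 44. The attrition step reproduces. The base of 20 cannot be checked because no standard deviation is given, but nothing here depends on it.

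2. **What rmANOVA keeps at T0-T1.** With two waves, the arm-by-time F statistic equals the square of the two-sample t statistic on T1 minus T0. A parent without T1 has no change score and drops out.
   - 10% missing at T1: 44 × 0.90 = 39.6 remain, 4.4 lost.
   - 5% missing (assumption, for range): 44 × 0.95 = 41.8 remain, 2.2 lost.
   - None missing, as in the pilot: 44 remain and the conflict does not arise.

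   The 10% is not tied to a wave. The first line assumes that it falls by T1.

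3. **Later waves.** Each added wave can only shrink a complete-case set, so a model that includes T2 to T4 keeps no more parents than the T0-T1 model. Loss per wave is not stated, so the number is unknown.

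4. **T0 set against randomised set.** Randomisation follows a completed baseline, so every randomised parent is in the T0 set. The reverse is not guaranteed, because allocation is limited to eligible parents. The difference is the number assessed at T0 but never allocated, which the article does not give.

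5. **Illustration of bias, not an estimate.** Suppose a fraction p of TI parents stop sessions, change only as controls do, **and** lack T1, while the remaining TI parents change by 11.3.
   - All-randomised difference = (1 − p) × 11.3 + p × 3.1 − 3.1.
   - p = 0.10: 10.48 − 3.1 = 7.38.
   - p = 0.20: 9.66 − 3.1 = 6.56.
   - Completer difference: 11.3 − 3.1 = 8.2, which is 8.2/7.38 = 1.11 to 8.2/6.56 = 1.25 times the all-randomised value.

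6. **What a mixed model changes in that scenario.** Its estimate of the TI mean at T1 is the completers' T1 mean plus a slope times the gap in mean T0 between all TI parents and TI completers. If dropout is unrelated to T0, that gap is zero on average and the model returns about 8.2 as well. A parent with T0 only adds little about change.

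**The case against.** The strongest reply is that the article nowhere says complete-case. Repeated-measures ANOVA run on imputed data would keep everyone, and missing-data handling is commonly left to a fuller document. That is fair, and the silence on imputation is not the fault raised here. What stands is that the one repeated-measures method the article fixes does not by itself produce the set it promises, under an attrition rate that the article itself assumes.

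Four stronger readings are tempting, and the article does not support them.

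- **That the effect will be overstated by 11 to 25%.** This needs 10 to 20% of TI parents both to stop sessions and to lack T1. The article plans T1 for both groups and makes no exception for parents who stop; a parent who stops but completes T1 stays in the ANOVA. The stopping rates have no source in the article.
- **That the bias favours TI.** WL dropout could push in either direction.
- **That only about 29 of 44 parents would remain.** That figure is 44 × 0.9⁴ = 28.9. It applies a trial-level 10% afresh at each of four waves, and it does not concern the primary T0-T1 contrast.
- **That unallocated parents will certainly enter the analysis.** T0 follows enrolment and consent, and the feasibility outcomes compare parents screened with parents enrolled, which suggests that screening may come first. If PSI screening precedes T0, the two sets may coincide. The participant flow figure is not available to settle this.

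It is also true that 22 per group already allows for the expected loss: 22 × 0.9 = 19.8, close to the planned 20. The issue is therefore the validity of the comparison and its label, not lost power.

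**Conclusion.** The point holds in a limited form. As written, the primary PSI comparison would be a complete-case analysis described as intent-to-treat. It would omit about 4 of 44 parents if the plan's 10% attrition falls by T1, and at least as many, by an unknown number, in any model that adds later waves. This rests on rmANOVA being run in its usual form without imputation.

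The T0-based definition is a slip in wording that should be corrected, though its practical effect may be nil. No direction or size of bias has been shown. The correction is worthwhile and cheap, but this is not a defect that by itself invalidates a trial presented as a pilot.

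**What to change.** - **Set.** Define the primary analysis set as all randomised parents, analysed in the arm to which they were allocated.
- **Primary model.** For PSI-SF, replace rmANOVA with a likelihood-based linear mixed model (REML, unstructured covariance, time and arm-by-time terms) fitted in SPSS to all observed data, with T0-T1 as the primary contrast.
- **Sensitivity analysis.** The model is valid only if data are missing at random, and it gains little from parents with T0 alone. Add one analysis that gives TI parents with missing T1 a WL-like change.
- **Label.** If a completer analysis is kept, do not call it intent-to-treat.

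The cost is a few sentences in the Statistical analysis section and slightly more programming. No new instrument, visit or participant is needed. The choice should be recorded before outcome data are analysed.

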### Primary research questions

To evaluate the potential efficacy of the randomized controlled trial (RCT), the primary research questions focus on changes in parenting stress:

Do parents in the TI group report a greater reduction in parenting stress index (PSI) scores following the 5-week intervention, compared to those in the WL group?

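### The named rmANOVA amounts to a change-score analysis of PSI with the baseline slope fixed at 1; ANCOVA on T0 PSI would be modestly more precise and would not move with chance baseline imbalance.

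*Protocol article*

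**What the plan says.** The Statistical analysis section of the protocol article lists the quantitative methods as "employing repeated measures ANOVA (rmANOVA"), t-tests and chi-squared tests. It describes the objective as change "before and after the intervention, measured by standardized questionnaires". The primary research question is also about change: "Do parents in the TI group report a greater reduction in parenting stress index (PSI) scores following the 5-week intervention", compared with the waitlist group.

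Four design statements bear on this choice:
- Eligibility rests on baseline PSI, "defined as a Parenting Stress Index (PSI) score ≥ 85 (critical high level").
- Baseline is complete before allocation: "Randomization will occur immediately following the completion of baseline assessment".
- "Stratification was not performed given the exploratory nature of the study and the anticipated sample size" (Randomization).
- "Baseline comparability between conditions will be examined on key demographic and clinical variables" (Randomization). No consequence for the analysis is attached to this.

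Under Data collection procedure, both arms are assessed at T1 before the waitlist arm starts the intervention. T0 to T1 is therefore the randomised comparison.

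**The concern.** A change score subtracts the whole baseline value, which is right only if a parent one point higher at T0 is expected to be one point higher at T1. Parents admitted because they scored at or above a cut-off tend to regress towards the mean, so the expected slope is below 1. Subtracting the full baseline then over-corrects: the arm that happens to start higher appears to improve more, whatever the treatment does.

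With about 22 parents per arm and no stratification, some difference in mean PSI at T0 is to be expected. Examining comparability describes that difference without removing its effect. Deciding on adjustment only after looking would make the analysis depend on the data. What is at stake is some precision, and the credibility of the single estimate that a small trial will produce.

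**Working it through.** **Inputs from the article.** Planned mean PSI decreases are 11.3 and 3.1, so the planned difference is 11.3 - 3.1 = 8.2. Alpha is 0.10 (sidedness not stated) and power 0.80. There are 20 per group before attrition and 22 after. Entry requires PSI of 85 or more.

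**Inputs assumed.** The documents give no SD, pre-post correlation or population mean. I take a normal population with mean 80-85 and SD 15, truncated at 85 at T0; equal SDs at T0 and T1 before selection, so the slope equals the correlation r; and r from 0.5 to 0.8.

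**1. The plan's own figure.** Twenty per group cannot be reproduced without an SD, and the role of the 10% non-inferiority threshold is unclear. For superiority with a difference of 8.2, 20 per group and 80% power, the noncentral t implies an SD of change of about 12.1 (one-sided 0.10) or 10.2 (two-sided 0.10). I use 12.1 below as a working value.

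**2. rmANOVA with two time points is the change-score test.** On a simulated data set with 20 per arm, the group-by-time F was 7.0209 and the squared t for change was 7.0209.

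**3. Effect of chance imbalance.** Let D be the baseline mean difference between arms, b the slope and τ the treatment effect. Given D:
- change score: expected estimate = τ + (b - 1)D
- ANCOVA: expected estimate = τ

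Simulation of 40,000 untruncated trials at 20 per arm gave shifts per unit of D of -0.60, -0.40 and -0.20 for the change score (r = 0.4, 0.6, 0.8), and about 0 for ANCOVA.

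**4. Precision with baseline truncated at 85.** The residual variance is 225(1 - r²). The variance of change is 225(1 - r²) + (1 - r)²V, where V is the truncated baseline variance.
- Mean 85: V = 225(1 - 2/π) = 81.8, SD 9.04.
- Mean 80: V = 66.8, SD 8.18.

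| r | 225(1 - r²) | Ratio ANCOVA/change, mean 85 | Ratio, mean 80 |
|---|---|---|---|
| 0.5 | 168.75 | 168.75/189.19 = 0.89 | 0.91 |
| 0.6 | 144.00 | 144.00/157.08 = 0.92 | 0.93 |
| 0.7 | 114.75 | 114.75/122.11 = 0.94 | 0.95 |
| 0.8 | 81.00 | 81.00/84.27 = 0.96 | 0.97 |

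**5. Power.** With the SD of change held at 12.1, 20 per group and the ANCOVA SD equal to 12.1 × √ratio:
- one-sided 0.10: 80% rises to 81-83%
- two-sided 0.10: 68% rises to 69-72%

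The gap between 80% and 68% comes only from sidedness, not from the choice of analysis.

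**6. Size of the shift.** Take mean 85 and 22 per arm. The SE of D is 9.04 × √(2/22) = 2.73 points.
- One SE: (1 - 0.8) × 2.73 = 0.5 to (1 - 0.5) × 2.73 = 1.4 points.
- Two SE (D = 5.45): 1.1 to 2.7 points.

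Against the planned 8.2, one SE is 7-17% and two SE is 13-33%. For scale, the SE of the effect is 12.1 × √(2/20) = 3.8.

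**The case against.** The strongest reply is that nothing here is invalid. The group-by-time test keeps its type I error and is unbiased over randomisation, and the conditional shift is already inside its standard error. That stands. It also means that lost precision and sensitivity to imbalance are one phenomenon seen from two sides, since the extra variance is (1 - slope)² times the variance of D. They should not be counted as two defects.

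A reader might infer that the plan ignores baseline PSI and leaves imbalance uncorrected. The documents do not support this: the primary question is about reduction, and T0 is a level of the repeated-measures factor. Baseline is used, but with an over-corrected slope.

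A reader might also expect the textbook gain, a variance ratio of (1 + r)/2, or 0.75-0.85 for r of 0.5-0.7. That formula assumes an unselected baseline. The entry threshold narrows the T0 distribution, and the gain shrinks to the figures in the table.

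The trial calls itself exploratory, and a condensed article may leave model terms to an analysis plan that is not shown. That is a reason not to fault a missing covariate list. It does not remove the point, which concerns the method the article names.

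**Conclusion.** The point holds as a modest, nearly free improvement. For T0-T1 PSI the named rmANOVA fixes the baseline slope at 1 in a sample where a lower slope is likely. ANCOVA would reduce the variance by about 3-11% and add about 1-4 points of power. It would also remove a conditional shift that is small in a typical allocation and reaches about 1.1-2.7 points in an unlucky one.

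The identity between rmANOVA and the change-score test, and the direction of the effect, are certain. The sizes rest on the assumed population mean, SD, correlation and SD of change. With precision gains this small, the better argument for the change is protection of one small trial's estimate against chance imbalance.

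**What to change.** Name as the primary analysis a linear model of T1 PSI-SF total on arm, with T0 PSI-SF total as a pre-specified covariate. Report the adjusted between-arm difference with its confidence interval. Treat each secondary scale that has a T0 value in the same way, using its own baseline. State this before outcome data are seen, so that adjustment does not depend on the comparability check.

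The cost is one or two sentences in Statistical analysis and one degree of freedom per model. No new data are needed, and the planned software can fit the model. Adding child age as a covariate is optional and not part of this point.
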